### Informed consent

2.9

The adult/s accompanying the child and the child will be approached by the RA who will engage using the process of whānaungatanga and values of whakamana and manaakitanga. The RA will introduce herself/himself, and explain the study in broad terms, saying what participation may involve, including matching the child's National Health Index (NHI) number against health outcome databases, plus giving the opportunity to ask questions and give time to consider participation.

Whānau will be provided a brief verbal summary of the study, including the main aims and processes of enrolment. Those that do consent to taking part in the study will be asked to sign consent forms. Those that do not consent will receive usual hospital care. At the time of consent, parent/s/caregivers will be asked if any other children in the household have been consented into the study. If so, the child will be allocated to the same intervention group (as outlined above). Participants will be informed they can withdraw their child, and/or themselves from the trial at any time, but that analysis of collected data will be on-going.

### Intervention procedure

2.10

The intervention will consist of a 24-section tool with screening questions and follow-up protocols for each question in accordance with the process shown in Figure 2. Intervention group patients and their whānau are invited to go over the Harti tool with the RA and provided with an information and activity booklet (whānau booklet). After engagement, RAs will go through the Harti tool on a tablet. RAs will read out questions in order and fill in answers for participants, in some cases participants may view questions and select responses themselves, if they prefer. The RA will follow established protocols to follow up on any identified areas of need. For example, if a child is not enrolled with a particular service, the RA will offer to assist with enrolment; if the patient or another child present or at home is identified to have a sore throat, then Rheumatic Fever prevention protocols will be followed. RA's will have equipment (cell phones and an iPad) to enable referrals and enrolments to take place at the bedside or in the interview room. The Harti RA will be trained in delivering high quality smoking cessation interventions for whānau and safe sleep devices including Pēpi Pods will be made available. If the whānau are not sure of the child's enrolment status (anecdotally a common occurrence), the Harti RA will match the patient’s National Health Index (NHI) number with selected databases and double check for access or check enrolment with the service over the phone or directly, e.g., oral health services.

### Control group

2.11

This group will receive usual hospital care and be offered the Marama satisfaction with care survey at the end of their hospital stay.

### Measures of effectiveness

2.12

A summary of each research hypothesis is listed in Table 2 and the details of how these will be examined is below.

**Table 2 T2:** The primary (1, 1a) and secondary endpoint hypotheses summarised for the trial outcome data.

Hypothesis number	Hypothesis
1	Use of the intervention will result in a 7% lower readmission risk at 30-days for children aged 0–4 admitted to hospital for the intervention group compared to the usual care group.
1a	Use of the intervention will result in a 5% lower readmission risk at 30 days for children aged under 12 months admitted to hospital for the intervention group compared to the usual care group.
2	The intervention will result in a 5% higher satisfaction with hospital experience score for the intervention group compared to the usual care group.
3a	Compared to usual care, the intervention assessment will result in at least a 50% increase in the full documentation of non-enrolment with a GP, non-enrolment in oral health services, not up-to-date oral health checks, incomplete immunisation (for age) and incomplete WCTO participation.
3b	Compared to usual care, the intervention assessment will result in at least a 25% increase in full compliance with GP enrolment, oral health service enrolment, oral health checks, immunisation and WCTO participation.
4	Compared to the UC group, the intervention group will have at least a 25% higher complete smoking cessation referral rate for households with a documented resident who smokes.
5	The intervention group will have at least a 25% higher complete Whare Ora referral rate compared with the UC group
6	The intervention group will have a significantly lower median cumulative length of hospital stay in all acute admissions in the 12 months following discharge from the index admission event compared with the UC group
7	The readmission rate in the intervention group will be 25% less than the readmission rate in the UC group.

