### Sample size calculation

2.8

We aim to recruit a total of 1,000 participants, of whom we expect approximately 40% will be Māori (based on current figures and expected acceptability of the research protocol). This sample has been calculated to ensure that there is sufficient statistical power to detect a 7% absolute reduction in the 30-day readmission risk in the intervention group for all children and a 12% absolute reduction in the 30-day acute readmission risk for Māori. Sample size calculations are based on a two-tailed 0.05 level of significance with 80% power. We assume that the acceptability of participation will be similar for Māori and non-Māori.

We will measure differences between the intervention and control groups in the primary endpoint (readmission risk) controlling for age, sex, residing in Hamilton, socioeconomic deprivation (NZiDep), and RA responsible for conducting the intervention. Analyses of the primary endpoint will be stratified by ethnicity.

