### Primary endpoint

2.13

The primary endpoint is the relative risk of an acute hospital readmission in the 30 days following discharge for intervention group patients compared with control group patients (Hypothesis 1). The relative risk of readmission rather than readmission rate ratio was chosen as the primary endpoint because risk (probability of readmission within specified period) is easier to measure as it just requires counting the first time a patient is readmitted. By only counting the first readmission we avoid patients with large numbers of readmissions having a disproportion impact on the endpoint measure. This also simplifies statistical analysis. We have included the hazard ratio of readmission as a secondary endpoint (see below).

We will measure ethnic-specific differences in the primary endpoint measures and differences according to a 30-day^2^ readmission risk for Māori and non-Māori patients (combined).

To determine the superiority limit for the purposes of sample size calculations it was considered that the Harti programme should deliver at least a 7% absolute decrease in overall readmission risk as this would be both clinically meaningful for tamariki and whānau and financially meaningful for the hospital. Furthermore, we have designed the study so that it has power to detect a 12% absolute decrease in the 30-day risk of readmission for the Māori population. It is not powered to detect differences in risk of readmission between Māori and non-Māori tamariki.

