### Additional pre-specified analyses of an exploratory nature, based on the primary endpoint

2.14

These will include the following:
➢The **hazard ratio** for (first) readmission in the intervention group compared with the control group. This compares time to the first readmission rather than just the fact of a readmission. As such, it can make use of varying lengths of follow-up time and may be more sensitive to the impact of the intervention. However, the use of the hazard ratio relies on the proportional hazards assumption, which is that the relative hazard of readmission remains constant over time.➢The **relative risk** of any readmission within 30 days of discharge, and from one to six months from the index admission event. This will examine whether the observed effect of the intervention on readmission rates occurs with a short or medium period. These analyses are exploratory as the trial has not been powered to detect difference within these time frames (although it may have adequate power to do so).➢A simple **Kaplan–Meir analysis** to compare the “survival” functions of intervention and control groups where survival in this case is taken to mean time following discharge without hospital readmission. For exploratory analysis of relative 6- and 12-month readmission risks this will also be used.➢Relative 30-day readmission risk in children aged less than 1 year at the time of their index admission (Hypothesis 1a). This outcome was added as a pre-specified analysis on the grounds that the interrupted time series analysis of the pilot suggested that the impact of the intervention is strongest (and possibly restricted to) this age group.

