### Data handling and monitoring

2.23

Analysis will be performed on an intention to treat basis. That is, endpoints will be compared for the two groups as defined from the point of randomisation to intervention or control group. For the primary endpoint, participants who are readmitted multiple times from each group will be included in the analysis only for the first (valid) occasion on which they are readmitted in the 12 months following the index admission.

Bivariate analyses comparing groups will test for statistical significance using the Chi Square test for differences in proportions. For the length of stay secondary endpoint where a difference in medians is to be tested, the Mann–Whitney *U* test will be used.

Although the randomised design is expected to yield balanced intervention and control groups in a study of this size, logistic regression analysis will be used for the primary and secondary endpoints to control for important confounding variables and to facilitate the assessment of interaction variables that increase or decrease the efficacy of the Harti tool. Statistical significance will be tested at the alpha level of 0.05. We will control for the false discovery rate in the secondary endpoints using the Benjamini–Hochberg method (39).

The study is not powered to detect ethnic differences in the impact of the intervention (effect modification). However, we will nevertheless conduct exploratory tests for effect modification with ethnicity (Māori/non-Māori), gender (male/female excluding other), and deprivation (as a dichotomised variable) using the Breslow Day test for homogeneity of odds ratio, and standard maximum likelihood methods (likelihood ratio tests) based on binomial regression models. We will assume an additive interaction for these analyses and report the relative excess risk due to interaction (RERI) where this is significant effect.

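### Hypothesis 1a (infants) is primary in the Table 2 caption but exploratory in section 2.14, and its 5% effect does not fit the stated reason for testing it

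*Protocol article*

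**What the plan says.** **Status of 1a.** The caption of Table 2 (section 2.12) is "The primary (1, 1a) and secondary endpoint hypotheses summarised for the trial outcome data". Section 2.13 defines the primary endpoint as the relative risk of acute readmission within 30 days of discharge, "compared with control group patients (Hypothesis 1"), and does not mention 1a. The abstract also names one primary endpoint, with no age restriction. Section 2.14 places 1a under the heading "Additional pre-specified analyses of an exploratory nature, based on the primary endpoint".

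**Error control.** Section 2.23 sets alpha at 0.05 and adds: "We will control for the false discovery rate in the secondary endpoints". It says nothing about more than one primary test.

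**Effect sizes.** Section 2.8 sizes the trial for "sufficient statistical power to detect a 7% absolute reduction in the 30-day readmission risk in the intervention group for all children" and for "a 12% absolute reduction in the 30-day acute readmission risk for Māori". Section 2.13 repeats both as absolute differences and presents the 7 points as the least the programme should deliver to be clinically and financially meaningful. For infants, Table 2 says: "Use of the intervention will result in a 5% lower readmission risk at 30 days for children aged under 12 months". Whether this 5% is absolute or relative, and where it comes from, is not stated.

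**Reason for 1a.** Section 2.14 says it was added because the interrupted time series analysis of the pilot suggested that "the impact of the intervention is strongest (and possibly restricted to) this age group".

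**The concern.** There are two separate inconsistencies.

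First, a reader cannot tell from the article whether a significant infant result would be a primary or an exploratory finding. This matters because the pilot rationale makes one pattern foreseeable: a null result in all children with a positive result in infants. Under the caption that pattern could be reported as success on a primary hypothesis. Under 2.13 and 2.14 it could not. Nothing in the multiplicity statement covers the case in which the caption is taken at its word.

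Second, the planned effect is smaller in the very subgroup where the effect is said to be largest. If infants respond most, or are the only ones who respond, an infant effect below the overall effect needs an explanation. None is given, so the 5% cannot serve as a benchmark for the 1a result.

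**Working it through.** **Inputs from the protocol article.** 7 points absolute for all children, two-sided 0.05, 80% power and 1,000 participants (2.8); 1:1 allocation (2.2); 5% for infants (Table 2). **Not given, so assumed:** the infant share of the sample, f, taken as 30% to 70%, and the control-arm 30-day risk.

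**1. The plan's own sample size.** Per arm, n = [1.96·√(2·p̄(1−p̄)) + 0.842·√(p₁(1−p₁) + p₂(1−p₂))]² / (p₁−p₂)². With an assumed control risk of 23%, p₁ = 0.23, p₂ = 0.16 and p̄ = 0.195:
- 1.96 × 0.5603 + 0.842 × 0.5581 = 1.568
- 1.568² / 0.07² ≈ 502 per arm, so 1,004 in total

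The stated 1,000 is therefore attainable at a control risk near 23%. It rests on Hypothesis 1 and the Māori figure, not on 1a.

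**2. Status and error rate.** The caption says 1 and 1a are primary, 2.13 says 1 only, and 2.14 says 1a is exploratory. If 2.13 and 2.14 govern, there is one primary test and the error is 5%. If the caption governs, there are two tests at 0.05. Infants are a subset of the whole sample, so the two test statistics have correlation of about √f under the null. The family-wise error is 1 − P(|Z₁| < 1.96 and |Z₂| < 1.96):

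| Infant share f | 30% | 40% | 50% | 60% | 70% |
|---|---|---|---|---|---|
| Family-wise error | 8.9% | 8.6% | 8.3% | 8.0% | 7.6% |

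The ceiling for two independent tests is 1 − 0.95² = 9.75%.

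**3. Effect sizes, reading the 5% as absolute.** Overall effect = f × (infant effect) + (1 − f) × (effect at age 1-4).
- Effect at age 1-4 needed for 7 overall with 5 in infants: (7 − 5f)/(1 − f).
- Overall effect if only infants benefit, by 5 points: 5f.
- Infant effect needed for 7 overall if only infants benefit: 7/f.

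| Infant share f | 30% | 40% | 50% | 60% | 70% |
|---|---|---|---|---|---|
| Age 1-4 effect needed (points) | 7.9 | 8.3 | 9.0 | 10.0 | 11.7 |
| Overall effect if infants only (points) | 1.5 | 2.0 | 2.5 | 3.0 | 3.5 |
| Infant effect needed for 7 overall (points) | 23.3 | 17.5 | 14.0 | 11.7 | 10.0 |

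The first row exceeds 5 at every share, so older children would have to gain more than infants, the reverse of 2.14. The direction does not depend on f: a weighted average of 7 with one component at 5 needs the other above 7.

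**4. Reading the 5% as relative.** The absolute infant effect is then smaller still. At a 23% risk it is 0.05 × 23 = 1.15 points, so the gap to 7 widens.

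**5. When "the impact of the intervention is strongest (and possibly restricted to) this age group" could still hold.** On the relative scale, infants show the larger proportional reduction if 5/p(infant) > 7/p(overall). With an overall control risk of 23%, this needs p(infant) < 5 × 23/7 ≈ 16%. The article gives no risk by age, so this can be neither confirmed nor excluded. It rescues only the first part of the rationale. If the effect were confined to infants, 5 points in them could not produce 7 overall at any share.

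**The case against.** **The body text largely settles the status.** Two sections and the abstract point to Hypothesis 1 as the only primary hypothesis, and the caption may group 1 with 1a only because both use 30-day readmission. That is the more natural reading, and it stands. It makes the 8-9% conditional, but the caption still says something different and needs correcting.

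**The Māori analysis.** A reader might infer that it is a third primary test, because it has its own power target, and that the error rate is higher again. The documents do not support this. Table 2 has no Māori hypothesis, no section calls that analysis primary, and being powered does not make a test co-primary.

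**The 7 points.** A reader might infer that the sample size is wrong because the pilot pattern implies a smaller overall effect. Section 2.13 sets the 7 points as a minimum worthwhile difference, not as a pilot estimate. Such a threshold may exceed what is expected without contradiction. This objection stands in full.

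**The scale.** The primary endpoint is a relative risk, 1a is defined in 2.14 as a relative 30-day risk, and the restriction to infants is worded tentatively. A smaller absolute effect in infants can therefore coexist with a larger relative one. This stands as a possibility, but only under an infant control risk that the article does not give.

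**Power of 1a.** A reader might also object that the trial is underpowered for 1a. Low power is no defect in an exploratory analysis, and any figure would depend on a control risk that is not stated.

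**Conclusion.** The concern holds as two inconsistencies in the article. The status conflict can be read directly from the text and needs no assumption. Its consequence is conditional: a family-wise error of about 8-9% if the caption governs (infant share 30-70%, each test at an unadjusted 0.05), and 5% if 2.13 and 2.14 govern. The documents do not establish that the trial's error rate is inflated, only that one of their statements would allow it.

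The effect-size conflict holds on the absolute scale, which sections 2.8 and 2.13 use for the 7 points. There, 5 in infants with 7 overall needs about 8-12 points at age 1-4, and an infant-only effect of 5 points gives about 1.5-3.5 overall. Whether the pilot effect was strongest in infants on the relative scale stays open. The point does not extend to the sample size of 1,000 or to the standing of the Māori analysis.

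**What to change.** 1. Correct the Table 2 caption so that Hypothesis 1 (all children, tested at 0.05) is the only primary hypothesis and 1a is labelled exploratory, in line with 2.13 and 2.14. A positive infant result beside a null overall result then cannot be reported as a positive primary result.
2. State for 1a whether the 5% is absolute or relative and what it is based on, for example a pilot estimate or a minimum worthwhile difference.
3. Reconcile that figure with the rationale in 2.14 and with Hypothesis 1. If the intended sense is a larger relative effect at a lower infant risk, say so and give the risk assumed.

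The cost is one caption, a sentence or two, and one restated or explained figure. Sample size, data collection and the planned Māori analysis do not change, and this point calls for no testing order for that analysis. What is given up is the option of claiming 1a as a primary result.

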### Baseline data collection

2.5

Recruitment and baseline data collection will be the responsibility of a RA who will be present, when possible, on the wards seven days per week. At the start of each day, a RA will generate a list of patients currently on the paediatric ward, screen them for eligibility, and check whether they have already been consented. RAs will check with the ward charge nurse to see if it is appropriate to approach the whānau of eligible patients. A record will be kept of all patients screened for eligibility to be approached and participate in the trial. Reasons for non-eligibility and/or refusal to participate will be recorded in a tracking sheet. Each RA will assure whānau that they have no obligation to provide a reason for non-participation in the trial. At the time of obtaining informed consent a baseline enrolment ascertainment form will be completed. The ascertainment form will record socio-demographic information (age, ethnicity and gender of tamariki patient and caregiver), method of transport to hospital, household size and structure, housing type and number of bedrooms, and level of material deprivation or NZiDep (33). The ascertainment form will be entered online using Qualtrics™ survey software.

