### Tobacco smoking cessation

2.18

The immediate reduction of the number of people who smoke is of huge importance for Māori and one of the key health targets for the Ministry of Health NZ. Adult smoking rates for Māori are 21.3%, higher when compared with other ethnics groups such as Pacific (18.1%), and European/Other (7.9%) (35). It is clear that parental or household smoking increases children's risk of developing respiratory infections, which commonly result in hospital admissions (36).

For this endpoint (hypothesis 4), we will use the proportion of parent/caregivers where a referral to stop smoking services was made during the hospitalisation period for cessation services. This will be calculated by sending a list of parent/caregiver NHI numbers of all participant parent/caregivers to the sole face to face smoking cessation provider (Once and For All). The provider will then confirm if a referral had been received for that NHI number during the period of hospitalisation or within 30 days of discharge from hospital for the index admission.

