### Referral to the Whare Ora healthy homes service

2.19

It is well established that good housing is particularly important for the first 9-months of life (37). The Growing Up In New Zealand study showed that poor housing was strongly associated with adverse health outcomes, even when controlling for income (37). Healthy homes initiatives have been shown to reduce acute hospital admissions in a NZ setting (26). The Whare Ora programme is a Waikato Healthy Homes initiative that was developed in 2016 to help whānau to create healthier, warmer, safer and drier homes. The service is free to eligible whānau and provides healthy homes education, products such as curtains, heaters, dehumidifiers and draught stoppers, and referral of families for further services by other providers (38).

Hypothesis 5 examines the difference between intervention and UC groups in the proportion of children for whom a Whare Ora referral was made within 30 days post-discharge. This will be calculated simply as the number of Whare Ora referrals in each group divided by the total number of eligible households (as some participants live in the same household) in that group. Any household can be counted only once in the numerator.

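### Hypothesis 4 (smoking cessation referral) has two incompatible definitions, and the Table 2 denominator would bias the comparison if used; Hypothesis 5 leaves household eligibility undefined

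*Protocol article*

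**What the plan says.** **Hypothesis 4, Table 2 (Section 2.12).** The target is "at least a 25% higher complete smoking cessation referral rate for households with a documented resident who smokes". The unit is the household, and the population is households where a smoker has been documented. Table 2 does not say where or when the documentation must be made.

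**Hypothesis 4, Section 2.18.** Here "we will use the proportion of parent/caregivers where a referral to stop smoking services was made during the hospitalisation period". The count is obtained by "sending a list of parent/caregiver NHI numbers of all participant parent/caregivers to the sole face to face smoking cessation provider". The unit is the caregiver and there is no smoker restriction. The provider then confirms whether a referral arrived "during the period of hospitalisation or within 30 days of discharge from hospital for the index admission", which is wider than the window in the first sentence.

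**Hypothesis 5.** Table 2 says "The intervention group will have at least a 25% higher complete Whare Ora referral rate compared with the UC group", with no eligibility condition. Section 2.19 introduces a proportion of children, then takes the number of referrals "divided by the total number of eligible households". It does not say what makes a household eligible or how that is determined.

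**Baseline data (Section 2.5).** "The ascertainment form will record socio-demographic information", together with transport, household size and structure, housing type, bedrooms and NZiDep. Household smoking is not listed.

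**Where the tool is used.** Smoking cessation and the healthy homes assessment are topics in the Harti tool (Table 1). Only the intervention arm receives the tool (Section 2.2).

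**The concern.** An analyst holding this protocol could compute Hypothesis 4 in two ways that differ in population, unit and window, and could reach different answers from the same referrals.

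The choice matters because only one version preserves the randomised comparison. Whether a smoker is documented is established after allocation. One research question in the Introduction is whether the tool increases documentation of need. For Hypothesis 3, Section 2.17 counts documentation in either the intervention assessment or the patient record, and the first of those exists in one arm only. If documentation has the same meaning in Hypothesis 4, the tool enlarges its own denominator by finding smokers who would otherwise go unrecorded. The arms would then be compared on differently selected households, contrary to the intention-to-treat comparison in Section 2.23. Section 2.17 avoids this for Hypothesis 3 by using external sources to establish need at admission. Table 2 states nothing similar for Hypothesis 4.

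For Hypothesis 5, an undefined eligibility condition leaves room for the same difficulty if eligibility were established differently in the two arms.

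**Working it through.** The protocol gives no calculation for Hypothesis 4 or 5, so there is no figure to reproduce. The check sets the two definitions side by side and then shows how far they can diverge.

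**Step 1: the two definitions**

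| Element | Table 2 | Section 2.18 |
|---|---|---|
| Unit | Household | Caregiver |
| Denominator | Households with a documented smoker | All participating caregivers |
| Source of denominator | Not stated | Participant list, both arms |
| Window | Not stated | Hospital stay; then hospital stay or up to 30 days after discharge |

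**Step 2: formula.** Let *s* be the share of households with a smoker, equal in both arms by randomisation. Let *D* be the share of those that are documented, and *R* the share of documented ones that are referred, with subscripts I (intervention) and U (usual care). Assume referrals arise only among documented smokers.

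- Ratio with the Table 2 denominator: R_I / R_U
- Ratio over all randomised: (s × D_I × R_I) / (s × D_U × R_U) = (D_I / D_U) × (R_I / R_U)

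The share *s* cancels. The two ratios agree only when D_I = D_U. Whenever D_I exceeds D_U, the Table 2 ratio is the lower one.

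**Step 3: one worked case.** The 1,000 participants at 1:1 (Sections 2.8 and 2.2) give 500 per arm, treated here as 500 households for simplicity. All other inputs are assumptions, not protocol figures: s = 30%, D_I = 95%, D_U = 50%, R = 40% in both arms.

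- Documented: 500 × 0.30 × 0.95 = 142.5 versus 500 × 0.30 × 0.50 = 75
- Referred: 142.5 × 0.40 = 57 versus 75 × 0.40 = 30
- Table 2 denominator: 57/142.5 = 40% versus 30/75 = 40%, ratio 1.00
- All randomised: 57/500 = 11.4% versus 30/500 = 6.0%, ratio 1.90

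**Step 4: range**, with D_I = 95% throughout. The last two columns assume that usual care documents fewer but more motivated smokers and refers 60% of them, against 40% in the intervention arm.

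| D_U | Table 2 ratio, R 40% v 40% | All randomised | Table 2 ratio, R 40% v 60% | All randomised |
|---|---|---|---|---|
| 30% | 1.00 | 3.17 | 0.67 | 2.11 |
| 50% | 1.00 | 1.90 | 0.67 | 1.27 |
| 70% | 1.00 | 1.36 | 0.67 | 0.90 |
| 95% | 1.00 | 1.00 | 0.67 | 0.67 |

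**Step 5: a check against the protocol's own expectation.** Hypothesis 3a expects documentation of preventive-care gaps to rise by at least 50%. If smoking documentation rose by the same factor (an assumption, since Hypothesis 3a does not cover smoking) and referral per documented smoker were unchanged, the ratio over all randomised would be 1.5 × 1.0 = 1.5. The Table 2 ratio would be 1.0, missing the 25% target of Hypothesis 4 despite half as many referrals again.

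**Step 6: Hypothesis 5.** No calculation is possible because eligibility is undefined. Section 2.19 notes that some participants share a household and counts each household once in the numerator, so the household can be taken as the intended unit. The missing piece is how eligibility is established.

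**The case against.** The strongest reply is that Section 2.12 presents Table 2 as a summary and refers the reader to the later sections for detail. On that reading Section 2.18 governs. It uses all participating caregivers and an external provider's records, and Section 2.24 blinds the person who matches NHI numbers to service databases. That version treats the arms alike. This stands: a reader might infer that the planned analysis of Hypothesis 4 is biased, and the document does not support that. The bias attaches only to the Table 2 denominator. What remains is that the two statements conflict, no precedence rule is given, and Section 2.18 itself contains two windows.

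Other points also stand:

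- A reader might infer that Hypothesis 5 has the same fault. Section 2.19 does not say that eligibility depends on need found by the tool. It could rest on the service's own criteria, or on the housing and deprivation data collected in both arms.
- A reader might infer that usual care records smokers only haphazardly. The protocol does not describe usual-care recording, and Section 2.18 calls smoking reduction a key health target.
- Non-caregiver smokers could enter the denominator but never the numerator only if the Table 2 denominator were joined to the Section 2.18 count. No section makes that combination.
- The size of the distortion rests on assumed inputs. With 70% usual-care documentation and higher usual-care referral, the ratio over all randomised is 0.90, so no benefit is hidden.

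**Conclusion.** The concern holds in a limited form. Hypothesis 4 has two incompatible definitions on the page, differing in population, unit and window. One is sound. The other would condition on a status that arises after randomisation and that the intervention is designed to change.

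If the Table 2 denominator were used, the error would run towards understating the effect, by the factor D_I / D_U. That factor is about 1.4 to 3.2 when usual care documents 70% down to 30% of smoking households and the intervention arm documents 95%. These documentation rates are assumptions, as is the premise that only documented smokers are referred. The factor is 1 if documentation is equal in both arms.

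For Hypothesis 5 the defect is an undefined eligibility rule and a measure introduced per child but divided by households. Differential ascertainment is possible there but not stated.

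Both are secondary endpoints and the primary endpoint is untouched. This should be fixed, but it is not a flaw in the trial design.

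**What to change.** **Hypothesis 4.** Amend Table 2 to match Section 2.18. Use all randomised caregivers, or all randomised households, in each arm as the denominator. Count the same people in numerator and denominator. State one window, index admission to 30 days after discharge, in both places.

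**Hypothesis 5.** Use all randomised households as the denominator, or define eligibility only from data held in the same way for both arms. State the household as the unit throughout Section 2.19, and align Table 2.

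**Cost.** With the all-randomised denominators, only wording changes. Section 2.18 already obtains the caregiver referrals, and shared households are asked about at consent (Section 2.9). The small downside is a lower absolute referral rate, because households without a smoker or without a housing need are included.

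New smoking or housing questions before randomisation are not needed. They would put tool topics to control families and could add to the contamination that Section 2.24 seeks to avoid.
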